**Methods and design:**

This study is a multicenter, prospective, randomized, evaluator-blinded non-inferiority trial. We aim to recruit 76 participants with post-stroke dysarthria. Eligible participants will be stratified based on the onset period of stroke into acute to subacute, and chronic phases. Participants will be randomized in a 1:1 to receive either a personalized digital speech therapy application or conventional therapy with a workbook for 60 min daily, 5 days a week, for 4 weeks. The primary outcome is the improvement in speech intelligibility. This will be measured by how accurately independent listeners can transcribe passages read by the participants. Secondary outcomes, which include speech function, will be evaluated remotely by speech-language pathologists. This includes the maximum phonation time, oral diadochokinetic rate, and percentage of consonants correct. Participants’ psychological well-being will also be assessed using self-report questionnaires, such as depressive symptoms (Patient Health Questionnaire-9) and quality of life (Quality of Life in the Dysarthric Speaker scale). The trial will also assess the feasibility, participant adherence, and usability of the application. Rigorous data collection and monitoring will be implemented to ensure patient safety.

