### Analysis

2.7

The primary objective of this trial is to investigate the non-inferiority of the intervention group compared to the control group in terms of changes in speech intelligibility from baseline to post-treatment. The hypothesis is as follows:

$$H_{0}:\mu_{t}-\mu_{c}<\delta \;vs\;H_{1}:\mu_{t}-\mu_{c}\geq \delta$$

Where *μt* is the mean change in speech intelligibility score in the intervention group using the digital speech therapy application, and *μc* is the mean change in the control group receiving conventional speech therapy. It is assumed that there is no difference between the two groups, and this study seeks to establish the non-inferiority of the groups. The non-inferiority margin *δ* is set at 19 points, based on the assumption that a difference of 1 to 19 points on the speech intelligibility scale is clinically non-inferior (45).

The sample size required for the non-inferiority trial was determined using a statistical formula (46). This involved setting the significance level (alpha) to 0.025 for a one-sided test and targeting a power of 80% (*β* = 0.2) (47) with a standard deviation of 24.9 (48). This calculation revealed that 28 participants are required for each group. A total of 56 participants are required for the trial. To account for a possible dropout rate of 30%, we aim to recruit a total of 76 participants, with 38 participants in each group.

$$n=\frac{2{\left(z_{\alpha }+z_{\beta }\right)}^{2}\sigma^{2}}{{\left(\mu_{t}-\mu_{c}-\delta \right)}^{2}}\approx 28$$

Analyses will be performed using SPSS software (version 27; IBM Corp., Armonk, New York). Descriptive statistics will summarize the demographic data and outcome measures. For interval estimates, 95% confidence intervals will be provided. An intention-to-treat (ITT) analysis will include all randomized participants. Additionally, we will conduct a per-protocol (PP) analysis which includes only participants who fully adhered to the intended protocol.

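### A recruitment target of 76 covers about 26% dropout, not the stated 30%; the effect on power is small

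*Protocol article*

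**What the plan says.** The sample-size paragraph in the Analysis section (2.7) of the protocol article gives these inputs: "setting the significance level (alpha) to 0.025 for a one-sided test", "targeting a power of 80" per cent, "with a standard deviation of 24.9", and a non-inferiority margin that "is set at 19 points". The true difference is taken as zero ("It is assumed that there is no difference between the two groups"). The printed formula is given as approximately 28 per group, and the text concludes: "A total of 56 participants are required for the trial". The next sentence sets the recruitment target: "To account for a possible dropout rate of 30%, we aim to recruit a total of 76 participants, with 38 participants in each group". It does not show how 56 becomes 76. The abstract repeats the target: "We aim to recruit 76 participants with post-stroke dysarthria".

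The same section says that the intention-to-treat analysis keeps everyone randomized and that a per-protocol analysis is added. Missing data are to be handled by multiple imputation and last observation carried forward. Table 2 schedules speech intelligibility at baseline and at 4 weeks only.

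**The concern.** The paragraph presents 56 as the number needed and 76 as the number that secures it under 30% dropout. A reader who multiplies 76 by 0.70 gets 53, which is below 56. So one of three figures (the requirement, the dropout rate or the target) does not belong with the other two.

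At stake is whether the dropout allowance can be taken at face value. Attrition matters in this trial. Section 2.2 makes a usage rate below 40% a ground for withdrawal, the Discussion names higher dropout as a possible limitation, and section 2.6.2 intends to use retention to inform the size of future studies. The allowance should therefore be stated correctly.

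**Working it through.** **Inputs** (all from section 2.7): one-sided alpha 0.025, so z = 1.960; power 80%, so z = 0.842; SD σ = 24.9; margin 19; true difference 0; required number 28 per group and 56 in total; dropout 30%; target 76, or 38 per group.

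**Step 1: the protocol's base sample size.**
n = 2(z_α + z_β)²σ² / 19² = 2 × (1.960 + 0.842)² × 24.9² / 19² = 26.96 per group, rounded up to 27.
The protocol states 28. The t-test (noncentral t) gives 80.1% power at 28 per group and 78.6% at 27, so 28 is the smallest size that reaches 80% by that method. The stated 28 and 56 are therefore acceptable.

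**Step 2: inflation for dropout.**
- From the stated requirement: 28/0.70 = 40 per group, 80 in total.
- Recruited minus lost: 38 × 0.70 = 26.6 per group; 76 × 0.70 = 53.2 in total, about 53.
- Dropout that 76 can absorb while keeping 56: 1 − 56/76 = 26.3%.

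**Step 3: does another convention give 76?**

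| Route | Per group | Total |
|---|---|---|
| 28/0.70 | 40 | 80 |
| 26.96/0.70 = 38.5, or 27/0.70 = 38.6, rounded up | 39 | 78 |
| 28 × 1.3 = 36.4, rounded up | 37 | 74 |
| 56 × 1.3 = 72.8, rounded up | – | 73 |

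None gives 76. The nearest values are 78, which sets aside the stated 28 and 56, and 74, which uses multiplication where division is needed.

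**Step 4: power at the number left.**
Normal formula: power = Φ(19 / [24.9 √(1/n₁ + 1/n₂)] − 1.960).
For 26 and 27: 19 / [24.9 √(1/26 + 1/27)] = 2.777, and Φ(2.777 − 1.960) = Φ(0.817) = 79.3%.
The t-test column uses the noncentral t with n₁ + n₂ − 2 degrees of freedom and the same noncentrality.

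| Complete cases | Normal formula | t-test |
|---|---|---|
| 28 + 28 = 56 | 81.5% | 80.1% |
| 27 + 27 = 54 | 80.1% | 78.6% |
| 26 + 27 = 53 | 79.3% | 77.8% |
| 26 + 26 = 52 | 78.6% | 77.0% |

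At 53 complete cases the shortfall from 80% is 0.7 points by the protocol's formula and 2.2 points by the t-test.

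**The case against.** The strongest reply is that nothing of consequence is lost. The protocol's formula needs only 26.96 per group, and 30% loss from 38 leaves 26.6, which is 0.36 of a participant short. On that formula power is 79.3%, and the gap to 80% is within rounding. The 2-point gap appears only under the t-test. That is a legitimate yardstick, because the t-test is the planned parametric comparison, but it is not the formula used for sizing. A gap of 2 points is also no larger than the effect of a slightly different SD: at 56 complete cases, an SD of 25.5 instead of 24.9 lowers t-test power from 80.1% to 78.2%. This reply stands as to size. A reader might infer from the dropout error that the trial is underpowered in any material sense, and the protocol's figures do not support that.

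A second reply is that 53 is not the intention-to-treat set, which keeps all 76 with missing values imputed. It is correct that 53 counts complete cases and should be labelled so. It does not rescue the sentence. The protocol itself inflates for dropout, so it treats 56 as the number needed after losses. With the outcome measured only at baseline and 4 weeks, imputation recovers little: carrying the last observation forward for someone who leaves simply enters zero change. The per-protocol set cannot keep all 76 either.

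A third reply is that the 30% is only a possible rate. That bears on the weight of the point. The sentence still claims that 76 accounts for that rate.

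**Conclusion.** The inconsistency is real and minor. From the stated 56 and 30%, the target would be 80; the stated 76 leaves about 53 complete cases and covers about 26% dropout. Power at 53 is about 79% by the protocol's formula and about 78% by the t-test, instead of 80%.

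These figures assume SD 24.9, margin 19, no true difference, one-sided alpha 0.025, losses spread nearly evenly over the groups (26 and 27), and an unadjusted complete-case comparison.

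A reader might also suppose that adjusting for baseline would bring power back above 80% without more participants. The document does not support that as a fact, because the gain depends on the correlation between baseline and week 4, which is not given. As an illustration, assume that 24.9 is the SD of the change score and that the variances at the two times are equal. Adjustment then multiplies the variance by (1 + r)/2, and t-test power at 53 is 84.0% for r = 0.70, 80.9% for r = 0.85, 79.8% for r = 0.90 and 78.8% for r = 0.95. No such claim should be relied on here.

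**What to change.** Keep the target of 76 and correct the sentence in section 2.7 in one of two ways:

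- State that recruiting 76 participants (38 per group) allows for about 26% dropout.
- Keep the 30% and state that at this rate about 53 participants have complete data and power is about 78–79% (t-test and normal formula respectively).

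Either costs one sentence and changes neither enrolment nor analysis; the abstract's 76 can stand. The only price is a slightly less favourable statement. If the sponsor prefers to keep both the 30% and the 56, the consistent target is 80 (40 per group). That means four more participants, and the abstract would need the same change.

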First, the Shapiro–Wilk test will assess of the normality of the distributions. Based on these results, the appropriate parametric (independent two-sample t-test) or non-parametric test (Mann–Whitney U test) will be chosen for between-group comparisons. Then, mixed repeated-measures analysis of variance (ANOVA) will evaluate the changes over time within subjects and between groups, with fixed effects for time, group, and their interactions. Mauchly’s test will check sphericity by applying the Greenhouse–Geisser, if necessary. For significant findings, Tukey’s HSD tests will conduct post-hoc analyses with Bonferroni correction to control for the overall type I error rate at 0.05. The benchmark for statistical significance is set at *p* < 0.05.

We will address missing data using multiple imputation techniques and the Last Observation Carried Forward (LOCF) method. This approach aims to minimize bias and ensure the robustness of efficacy outcomes (49). Subgroup and sensitivity analyses will be conducted to explore the effects of participant characteristics and institutional factors on the primary efficacy results. In addition to the primary analysis, we will conduct subgroup analyses to examine the efficacy of our digital speech therapy application in various settings. Subgroup analyses include comparing its use during hospitalization with post-discharge home use. These analyses aim to provide a deeper understanding of how the setting influences the effectiveness of the therapy.

Furthermore, additional subgroup analyses will focus on the effects of the interventions across different stroke phases. Since participants are stratified based on the onset period of their stroke into acute to subacute, and chronic phases, these subgroup analyses will explore how the efficacy of the intervention varies between these two distinct stroke phases. We will perform regression analyses within each group stratified by the stroke onset period. If the statistical analysis reveals significant mean differences between various groups, post-hoc tests will be conducted to identify the specific groups among which these differences exist. This approach will provide valuable insights into whether the timing of a post-stroke intervention influences the efficacy of digital speech therapy. No interim analyses are planned to maintain the integrity of the non-inferiority margin or control for type I error rate.

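### The named between-group tests ask whether the arms differ, not whether the app is within 19 points of the workbook; no rule links the promised 95% CI to the margin, and the Mann–Whitney branch leaves the mean hypothesis untested

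*Protocol article*

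**What the plan says.** Everything on this point is in section 2.7 (Analysis) of the protocol article.

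- **Objective:** "The primary objective of this trial is to investigate the non-inferiority of the intervention group compared to the control group", judged on change in speech intelligibility from baseline to post-treatment. The hypothesis is written on the difference between two mean changes.
- **Margin:** "set at 19 points, based on the assumption that a difference of 1 to 19 points on the speech intelligibility scale is clinically non-inferior".
- **Design error rate:** the sample size came from "setting the significance level (alpha) to 0.025 for a one-sided test", with 80% power, "with a standard deviation of 24.9" and no true difference. The result is 28 per group, raised to 38 for dropout.
- **Intervals:** 95% confidence intervals are to be given for interval estimates. Nothing more is said about their use.
- **Tests:** after a Shapiro–Wilk test, "Based on these results, the appropriate parametric (independent two-sample t-test) or non-parametric test (Mann–Whitney U test) will be chosen for between-group comparisons". A mixed repeated-measures ANOVA (time, group, interaction) comes next, with Mauchly's test and a Greenhouse–Geisser correction if needed. Significant findings lead to Tukey "post-hoc analyses with Bonferroni correction to control for the overall type I error rate at 0.05".
- **Threshold:** "The benchmark for statistical significance is set at" p < 0.05, with no side given.

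The description of the tests mentions neither the margin nor a one-sided level. The margin comes up again only in the sentence that rules out interim analyses.

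**The concern.** A non-inferiority claim needs a test whose null is that the app is worse by at least the margin or, equivalently, a confidence limit set against the margin. In standard form, the t-test, the Mann–Whitney test and the ANOVA interaction all take no difference as the null. A non-significant result does not show non-inferiority, and a significant one does not exclude it.

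The Mann–Whitney branch is the more serious part. It compares distributions, while the hypothesis and margin concern means. A normality pre-test on the trial data would thus decide whether the primary question is addressed. Non-normality is a realistic prospect: the outcome is a percentage of words correctly transcribed (section 2.6.1), and both mild-to-moderate and severe dysarthria are enrolled (section 2.2).

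At stake is the trial's only primary claim. The one threshold given for reading results belongs to another question.

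**Working it through.** **Inputs, all from section 2.7:** margin 19 points, SD 24.9, one-sided alpha 0.025, power 80%, true difference 0, 28 evaluable and 38 recruited per group.

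**Assumptions:** 24.9 is taken as the SD of change in each arm. The margin is read as −19 for app minus workbook. The hypothesis is printed without the minus sign, but with no true difference the sample size formula gives the same result for either sign.

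**1. The plan's own figure.** n = 2(z₀.₉₇₅ + z₀.₈₀)² σ² / 19² = 2 × (1.960 + 0.842)² × 620.01 / 361 = 26.96, so 27 per group by the normal formula. With the t distribution, power is 78.6% at 27 and 80.1% at 28. The stated 28 is reproduced, so the trial is sized for a one-sided 0.025 non-inferiority test.

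**2. Precision.** SE = 24.9 × √(2/n).
- n = 28: SE 6.65, 95% CI half-width 13.3.
- n = 38: SE 5.71, 95% CI half-width 11.4.

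**3. Where the two questions part.** If the observed SD equals 24.9 and n = 28, the difference test is non-significant when the observed difference lies within ±13.3. Non-inferiority needs an observed difference above −19 + 13.3 = −5.7. A difference between −13.3 and −5.7 is therefore non-significant and still fails non-inferiority.

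**4. Probabilities by noncentral t.** The difference test is two-sided at 0.05. The margin rule asks for a 95% CI lower limit above −19.

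| True difference | n per group | p ≥ 0.05 for difference | Lower limit above −19 |
|---|---|---|---|
| 0 | 28 | 95.0% | 80.1% |
| −10 | 28 | about 69% | 26.4% |
| −19 | 28 | 19.9% | 2.5% |
| 0 | 38 | 95.0% | 90.7% |
| −19 | 38 | 9.3% | 2.5% |

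The 19.9% is the type II error of the difference test at −19: 1 − 0.801.

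**5. Mann–Whitney.** In simulated normal data with 28 per group (4,000 trials), the unshifted test was significant in 4.3% of trials at a true difference of 0 and 77.9% at −19. It behaves as a difference test too, and it gives no estimate of the mean difference to set against 19 points.

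**6. ANOVA.** Table 2 schedules intelligibility at baseline and 4 weeks only. With two time points, the group-by-time test is the t-test on change, so it has the same null and adds nothing towards the margin.

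**The case against.** - **The tests are not labelled primary, and the same paragraph must serve the secondary outcomes, for which difference tests are ordinary.** True, but the article gives no other between-group test for the primary outcome.
- **The t-test route is nearly right already.** This stands. The t-test comes with a CI for the mean difference, a 95% CI is promised, and its lower limit set against −19 is exactly the one-sided 0.025 test used for sizing. On that route only the decision sentence is lacking. It would be too strong to say that the planned data or the t-test cannot decide non-inferiority.
- **An article may leave the decision rule to the full protocol or SAP.** If the rule were merely absent, this would settle the matter. But the article does name the tests, a threshold and a data-driven switch to Mann–Whitney, and these do not match its own hypothesis.
- **Alpha.** A reader might infer that p < 0.05 contradicts one-sided 0.025 and doubles the error to 5%. The text does not support that. Read two-sided, as is usual, 0.05 agrees with one-sided 0.025. The doubling needs a one-sided margin test read at 0.05, and the article gives 0.025 for the one-sided test.
- **The 20% figure.** A reader might infer that the plan carries a 20% false non-inferiority rate. It does not say that p ≥ 0.05 means non-inferiority, so the figure is conditional. It also falls to 9.3% at 38 per group, the nominal size of an analysis of all randomized participants.
- **Mauchly, Greenhouse–Geisser, Tukey and Bonferroni.** With two time points and two arms these are redundant, but they do not change the primary result.

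**Conclusion.** The point holds as a mismatch between stated hypothesis and stated analysis. The between-group tests in section 2.7 are unshifted tests of no difference, and no sentence ties the promised 95% CI to 19 points. If Shapiro–Wilk rejects normality, the named test does not address the difference in mean change.

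The size is conditional. If a non-significant difference were read as non-inferiority, the false-claim rate at a true difference of −19 would be 19.9% (28 per group) or 9.3% (38 per group), against the planned 2.5%. This rests on SD 24.9 for change, normal data and a margin of −19. The protocol does not state that reading, but gives no rule that prevents it. The defect is in the decision rule and the choice of test; the design, the data collected and the sample size are not affected.

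**What to change.** For the primary outcome, replace the test-selection text with one analysis: the mean difference in change in intelligibility, app minus workbook, with a two-sided 95% CI. Declare non-inferiority only if the lower limit is above −19, and say that this is the one-sided 0.025 test used for sizing.

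Do not switch to Mann–Whitney on a normality pre-test for this outcome. If non-normality is a concern, add a bootstrap CI of the mean difference as a sensitivity analysis. State that the p < 0.05 benchmark is two-sided and applies to difference tests. The sphericity and post-hoc steps can be dropped for the primary outcome as tidying.

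The cost is wording in the protocol and SAP, best settled before unblinded data are seen. With 28 per group the rule gives 80.1% power at no true difference and 2.5% error at the margin, so the sample size does not change.

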### Randomization

2.3

Participants will be randomly allocated in a 1:1 ratio to either the intervention group or control group. An independent third-party entity will oversee the randomization process to ensure impartiality.

Additionally, the trial will stratify participants based on the onset period of their stroke: acute to subacute phase (within 1 month of onset) and chronic phase (from 1 month to 6 months of onset) (24). After confirming participants’ eligibility, we will assign each participant a sequential number for group allocation. For each stratum, we will actively allocate participants in a 1:1 ratio to either the intervention or the control group. A secure computerized system will generate an unpredictable and concealed allocation sequence. A blinded researcher will manage this sequence in opaque envelopes, which will be opened after the participant’s enrollment and baseline measurements are complete.

To ensure group balance and methodological rigor within each stratum, we will use permuted blocks of sizes two and four (25). The block size and allocation sequence details will remain confidential and inaccessible to the team members involved in recruitment, treatment, and assessment until the conclusion of the study.

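### The listed between-group analyses of speech intelligibility adjust for neither baseline score nor stroke phase, which gives up precision the trial could have at no cost

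*Protocol article*

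**What the plan says.** All references are to the protocol article.

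- **Objective (Analysis, 2.7).** Non-inferiority is to be shown "in terms of changes in speech intelligibility from baseline to post-treatment".
- **Between-group methods (2.7).** A Shapiro–Wilk test selects a two-sample t-test or a Mann–Whitney U test. A mixed repeated-measures ANOVA follows, "with fixed effects for time, group, and their interactions". No other term is listed.
- **Stratification (Randomization, 2.3).** Here "the trial will stratify participants based on the onset period of their stroke", in two strata: within 1 month, and 1 to 6 months.
- **Use of phase in the analysis (2.7).** Phase appears only in subgroup analyses and in regressions run within each group. Sensitivity analyses on participant and institutional factors are mentioned without a model.
- **Timing (Table 2).** Intelligibility is assessed at baseline and at 4 weeks only.

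**The concern.** Three features of this trial make the omission matter.

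1. **Baseline is likely to predict change.** Section 2.2 admits patients from slurred but understandable speech to mostly unintelligible speech, and section 2.6.1 scores the outcome as a percentage of words correctly transcribed. Patients near the top of the scale have little room to improve, and regression to the mean acts at both ends. Subtracting baseline does not remove that dependence. With about 28 per arm, a chance imbalance in baseline carries into the observed difference in change.
2. **Phase is probably prognostic.** The trial stratifies on it, and the Discussion argues that early treatment improves outcome. If a prognostic stratification factor is left out of the model, its variance stays in the residual and the standard error is too large.
3. **The interval decides the result.** In a non-inferiority trial, avoidable width translates directly into a lower chance of success. With 30% dropout from 38 per arm, 38 × 0.70 = 26.6 remain, fewer than the 28 that the calculation requires.

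**Working it through.** **Inputs, all from section 2.7:** "setting the significance level (alpha) to 0.025 for a one-sided test"; "targeting a power of 80" per cent; "with a standard deviation of 24.9"; a margin that "is set at 19 points"; and a true difference of zero ("It is assumed that there is no difference between the two groups"). The protocol does not say whether 24.9 is the SD of change or of a single score.

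**Step 1. Reproduce the plan's figure.** n = 2(1.960 + 0.842)² × 24.9² / 19² = 26.96, so 27 per group against 28 stated. This is close enough. Power at 28 per group is 81.5% by the normal approximation and 80.1% by the noncentral t. The noncentral t is used below.

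**Step 2. Does the ANOVA adjust for baseline?** No. With two time points the group-by-time F equals the squared t for change. On a simulated data set both were 1.0531.

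**Step 3. Variance with baseline as a covariate.** Assume equal SD σ at both times and correlation ρ.

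- Change: 2σ²(1−ρ)
- ANCOVA: σ²(1−ρ²)
- Ratio: (1+ρ)/2, whichever quantity 24.9 measures

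**Step 4. Power if 24.9 is the SD of change.** The ANCOVA SD is 24.9 × √((1+ρ)/2). The values of ρ are assumptions.

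| ρ | Variance ratio | ANCOVA SD | Power, 28 per group | Power, 26.6 per group |
|---|---|---|---|---|
| unadjusted | 1.00 | 24.9 | 80.1% | 77.9% |
| 0.3 | 0.65 | 20.1 | 93.5% | 92.3% |
| 0.5 | 0.75 | 21.6 | 89.9% | 88.3% |
| 0.7 | 0.85 | 23.0 | 86.0% | 84.2% |
| 0.8 | 0.90 | 23.6 | 84.0% | 82.1% |
| 0.9 | 0.95 | 24.3 | 82.0% | 80.0% |

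Charging the two extra degrees of freedom lowers these by at most 0.1 point.

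**Step 5. Power if 24.9 is the SD of a single score.** The change SD is 24.9 × √(2(1−ρ)) and the ANCOVA SD is 24.9 × √(1−ρ²). At 28 per group:

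| ρ | Change SD | Power, change | ANCOVA SD | Power, ANCOVA |
|---|---|---|---|---|
| 0.3 | 29.5 | 66% | 23.7 | 84% |
| 0.5 | 24.9 | 80% | 21.6 | 90% |
| 0.7 | 19.3 | 95% | 17.8 | 97.5% |
| 0.8 | 15.7 | 99.3% | 14.9 | 99.7% |

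**Step 6. Phase.** If phase explains 10% of the remaining variance (assumed), omitting it inflates the standard error by √(1/0.9) = 1.054, about 5%.

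**Step 7. Simulation.** 28 per arm, 4,000 runs per case (Monte Carlo error about √(0.8 × 0.2/4000) = 0.6 points), with 24.9 as the SD of change within phase. The adjusted model has baseline and phase.

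| ρ | Phase difference in recovery (assumed) | CI half-width, unadjusted / adjusted | Power, unadjusted / adjusted |
|---|---|---|---|
| 0.5 | 0 | 13.2 / 11.6 | 79.7% / 89.6% |
| 0.7 | 0 | 13.3 / 12.4 | 79.2% / 84.0% |
| 0.9 | 0 | 13.3 / 13.1 | 80.2% / 81.1% |
| 0.5 | 20 points | 14.4 / 11.6 | 75.8% / 89.6% |
| 0.7 | 20 points | 14.4 / 12.4 | 75.8% / 85.9% |
| 0.9 | 20 points | 14.4 / 13.1 | 74.5% / 80.6% |

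A second simulation gave adjusted power of 89.2% at ρ = 0.5 and 85.1% at ρ = 0.7.

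**The case against.** The strongest reply is that this is a matter of efficiency, not an error. Under stratified 1:1 randomisation the unadjusted difference in change is unbiased, its standard error already covers chance baseline imbalance, and leaving out the stratum errs on the conservative side. It does not make a false claim of non-inferiority more likely. The t-test also matches the sample size formula, which is unadjusted. All of this stands, and it is why the point concerns precision only.

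The size is also uncertain. Neither ρ nor the phase effect is in the protocol, and 24.9 is not defined. On the single-score reading with ρ of 0.7 or more, power is already at least 95% and adjustment adds little. The formula treats the covariate slope as known, so it slightly flatters ANCOVA: at ρ = 0.7 it gives 86.0%, while simulation gives 84.0% to 85.1%. These limits stand too. They change how much is gained, but the ratio (1+ρ)/2 is below 1 for any ρ below 1 on either reading.

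Finally, covariates are often settled in an analysis plan, and phase does appear in planned subgroup work. Here, though, the article lists the model terms explicitly, and separate estimates by phase or regressions within an arm do not give a phase-adjusted difference between arms. This part does not remove the point.

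**Conclusion.** The point holds. The listed between-group methods use baseline only by subtraction and leave out the stratification factor. The cost is avoidable width in the deciding interval.

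If 24.9 is the SD of change, adjusting for baseline alone removes 15% to 35% of the variance for ρ from 0.7 down to 0.3. That brings power at 28 per group from 80% to between 86% and 94%, and at 26.6 per group from 78% to between 84% and 92%. At ρ = 0.9 the gain is about 2 points, unless phase is prognostic. With an assumed 20-point phase difference, the unadjusted analysis falls to about 75% power while the adjusted one stays at 80.6% or more.

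These figures assume equal SDs at both times, a true difference of zero and values of ρ that the protocol does not supply. The change is worth making but is not critical to the trial's validity.

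**What to change.** Before unblinding, name one primary model: ANCOVA of week-4 intelligibility on arm, baseline intelligibility and stroke phase (within 1 month; 1 to 6 months). Declare non-inferiority if the lower limit of the 95% CI for the adjusted difference (application minus control) lies above −19. This also gives an estimate on the scale of the margin, which the Mann–Whitney branch does not.

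Keep the unadjusted difference in change as a sensitivity analysis. For consistency, use the same model form, each outcome with its own baseline, for maximum phonation time, diadochokinetic rate, consonants correct, PHQ-9 and QOL-Dys. State whether 24.9 is the SD of change or of a single score.

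The cost is wording in the analysis plan and two degrees of freedom. No extra data or participants are needed, since baseline score and phase are already recorded for everyone.

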Subsequently, the participants will undergo a comprehensive assessment for post-stroke dysarthria. Psychological well-being questionnaires will also be administered to assess depression and quality of life. Participants will engage in the post-evaluation phase 4 weeks after the baseline assessment. We will repeat the speech assessments and psychological questionnaires from the baseline evaluations. Additional evaluations of usability and adherence rates will be conducted.

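### LOCF with only a baseline and a 4-week measurement scores every dropout as zero change, and if it feeds the ITT non-inferiority test with similar dropout in both arms, false non-inferiority rises from 2.5% to about 16–22%

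*Protocol article*

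**What the plan says.** Section 2.7 (Analysis) deals with missing data in one statement: "We will address missing data using multiple imputation techniques and the Last Observation Carried Forward (LOCF) method". It presents the pair as a way to limit bias and gives neither method a primary or a sensitivity role.

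The primary endpoint is the change in intelligibility from baseline to post-treatment. The ITT set holds everyone randomized, and a per-protocol analysis is run in addition. Table 2 (section 2.6) marks intelligibility at baseline and at 4 weeks only; the close-out column carries system usability alone. The text of 2.6 agrees: "Participants will engage in the post-evaluation phase 4 weeks after the baseline assessment".

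The sample size paragraph in 2.7 plans for substantial loss: "To account for a possible dropout rate of 30" percent, the target is 76 participants, 38 per group.

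**The concern.** LOCF uses the last outcome measured before the missing one. With two scheduled measurements that is always the baseline, so the imputed change is 0 in either arm, whatever the participant's course. The application's own speech tasks (section 2.5.1) serve treatment planning and are not outcome assessments in Table 2, so they provide no intermediate value.

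In a superiority trial, pulling both arms towards the same value usually costs power. In a non-inferiority trial it favours the claim under test, because a real deficit is diluted. LOCF also counts the filled-in zeros as observed data, so the interval is too narrow. At the planned dropout, nearly a third of the ITT data could be affected. The error at stake is concluding that the application is non-inferior when it is worse by the full margin.

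**Working it through.** **Inputs from section 2.7.** Level: "setting the significance level (alpha) to 0.025 for a one-sided test". Power: "targeting a power of 80" percent. Spread: "with a standard deviation of 24.9", which I take as the SD of the change score because the article does not say. The margin "is set at 19 points"; I read it as a lower limit of −19 for app minus control. On the true difference: "It is assumed that there is no difference between the two groups". Allocation is 1:1, with 38 per arm and 30% dropout.

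**Assumed, not in the article.** Mean change in the control arm (gain) of 0 to 40 points; dropout independent of outcome.

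**Step 1: the plan's own figure.** n = 2(1.96 + 0.842)² × 24.9² / 19² = 26.96, so 27 per group by the normal approximation. With the t distribution, 28 per group gives power 0.801 and 27 gives 0.786. The stated 28 is reproduced.

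**Step 2: what LOCF estimates.** Let d_t and d_c be the dropout proportions and μ_t and μ_c the mean changes in the app and control arms. With missing changes set to 0, the expected difference is

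(1 − d_t)μ_t − (1 − d_c)μ_c.

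With equal dropout d this is (1 − d)(μ_t − μ_c). For a true difference of −19 and d = 0.30 it is 0.7 × (−19) = −13.3, a shift of 5.7 points towards non-inferiority.

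**Step 3: false non-inferiority, equal dropout.** Simulation at a true difference of −19, 38 per arm; non-inferiority is declared if the lower limit of the t-based 95% interval lies above −19. Ranges cover control gains of 0 to 40.

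| Dropout in both arms | LOCF |
|---|---|
| none | about 2.5% |
| 10% | 5–6% |
| 20% | 9–11% |
| 26% | 13–17% |
| 30% | 16–22% |

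The 26% row is the loss that 76 recruited can absorb while keeping 56: 1 − 56/76 = 0.263. On complete cases the error stayed at about 2.3–2.8% throughout.

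**Step 4: unequal dropout, LOCF.**

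| App / control dropout | Gain 10 | Gain 20 | Gain 30 | Gain 40 |
|---|---|---|---|---|
| 40% / 20% | 21% | 11–12% | 5% | 2% |
| 20% / 40% | 23% | 35% | 44% | 50% |

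For gains of 10 to 30 the range is thus about 5% to 44%. From the formula in step 2, the expected difference falls below −19 only when the control gain exceeds 19·d_t/(d_t − d_c). At 40% against 20% that is 19 × 0.4/0.2 = 38 points. In the extreme case of 50% app and 10% control, the error is 5% at a gain of 20 and 0.7% at a gain of 30.

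**Step 5: multiple imputation on the same data.** Dropout depends on baseline, the correlation of baseline with change is assumed to be −0.4, and imputation is by arm with Rubin's rules. At 30% dropout in both arms and gains of 10 to 30, imputation gave 1.9–2.4% and LOCF 20–24%.

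**Step 6: interval width at 30% dropout.** Complete cases: 38 × 0.7 = 26.6 per arm, so the half-width is about 2.01 × 24.9 × √(2/26.6) = 13.7 points. Under LOCF the two arm variances sum to 2 × 0.7 × 24.9² + 0.21[M² + (M − 19)²] for control gain M. With t = 1.99 and 38 per arm, the half-width is 9.7 points at M = 10 and 10.6 at M = 30.

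**The case against.** **LOCF may not decide anything.** Multiple imputation is named too, and named first. If it carries the primary test, the error stays near nominal. A reader might infer from the section that the trial's type I error is inflated as planned; the article does not support that. Nor is the missing order of the two methods a fault in itself, since a statistical analysis plan may settle it. What stands is that the article names, on a par with a suitable method, one that does not suit this endpoint. Demoting LOCF to a sensitivity analysis would not make it useful: with similar dropout it leans towards non-inferiority, so its agreement would reassure falsely.

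**The direction is not fixed.** A reader might also infer that LOCF always draws the arms together. It does not. The Discussion anticipates that missing supervision may raise dropout with the app, and step 4 shows the error falling as the control gain rises in that case. This stands as a limit. But at 40% against 20% the error is still about double nominal at a gain of 30, and it goes below nominal only past 38 points. An error rate that turns on unknown arm means is no safeguard.

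**The per-protocol analysis should not contain LOCF-filled dropouts.** True, but it is described as additional, the article states no rule that both sets must agree, and it has its own selection problem.

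**Zero change may be right for dropouts.** If so, LOCF would not be biased for them. The Introduction's figures, 22–60% with dysarthria in the first week and about 35% still affected after 6 months, suggest change over time, and one stratum is enrolled within a month of onset.

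**The simulation uses a t-interval.** Section 2.7 chooses between a t-test and Mann–Whitney by a Shapiro–Wilk test. With 30% exact zeros that test rejected in at least one arm in 89–95% of runs (gains 10–30), so on LOCF-filled data the rank test would usually be chosen, and its error was not simulated. Also, with a gain of 10 or less the app arm worsens on average, which is less plausible with content matched between arms. At a gain of 30 the rate is still about 19%.

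**Conclusion.** The concern holds in conditional form. LOCF in this two-measurement design sets every dropout's change to 0. If it feeds the ITT non-inferiority test and dropout is similar in both arms at the planned 30%, a true deficit of 19 points is estimated as 13.3, and the one-sided error is roughly six to nine times its nominal 2.5%. With unequal dropout the error depends on the arm means and is usually above nominal.

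The sizes rest on 24.9 being the SD of change, a t-interval, dropout unrelated to outcome, and assumed control gains. The zero change itself needs none of these; it follows from Table 2. The article does not establish that the primary conclusion will rest on LOCF, and this point does not claim it.

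**What to change.** In section 2.7, or in the analysis plan before unblinding:

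1. Remove LOCF from the non-inferiority test.
2. Name multiple imputation under missing-at-random as the single primary method for the ITT analysis, done by arm with baseline intelligibility and stroke phase as predictors. With about 27 observed participants per arm at 30% dropout, the imputation model should stay this small.
3. In place of LOCF as a sensitivity analysis, run a delta-adjusted tipping-point analysis that lowers the imputed app-arm values in steps, down to a shift of −19. Report the shift at which non-inferiority is lost.

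No visit or recruitment target changes. The cost is wording, a few extra runs and a wider interval: a half-width of up to about 13.7 points at 30% dropout, against about 10 to 11 under LOCF. Imputation that uses baseline may recover part of the difference. The extra width is not a loss of real precision, since LOCF obtains its narrower interval by treating invented zeros as data.
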